### Study Sample and Inclusion Criteria

This study is a multiarmed randomized controlled trial that was conducted with a sample of women of reproductive age from Lilongwe, Malawi. The study comprised a baseline survey, randomization into 1 of 3 treatment arms or 1 control arm, and the implementation of a 2-month intervention. One follow-up survey was conducted after the intervention and was administered to women either at the clinic or on the phone. If participants could not be reached in either way, then a home visit was paid to the households. Figure 1 outlines the general framework of the entire field experiment.

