### The Intervention

#### Intervention Protocols

All women who consented to participate in the study (T0-T3) were offered a free, private family planning counseling session, which included a risk assessment for contraceptive methods and detailed information on methods switching, side effects associated with each method, and the benefits of contraception and birth spacing. A precounseling survey was administered to each woman, where they were asked to confirm their personal information, including, but not limited to, pregnancy status, current contraceptive use, and preferences for fertility and contraception. During counseling sessions, counselors provided women with information on the range of modern and natural family planning methods based on their respective intervention assignments. Strategies on how to communicate family planning messages with partners and on how to increase partner awareness were conveyed during the sessions. The counseling session lasted no more than 1 hour and was administered in a private room by a counselor who was trained to provide family planning and reproductive health services. To facilitate an effective and open dialog with women during the counseling session, only female counselors were hired. Counselors were hired by IPA Malawi, held a nursing degree, and were trained on the range of counseling protocols over a week. We enlisted the support of the Malawi RHD and several international nongovernmental organizations who work on family planning, including Population Services International (PSI), BLM, the Family Planning Association of Malawi, and FHI360, to help us develop training materials and counseling resources. We also collaborated with the Malawi RHD, BLM, and PSI to assist with counselor training.

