### Postcounseling Survey

#### Survey Instrument and Rollout

Following the counseling session, counselors conducted a brief survey with all women to assess their experiences with the counseling service. Multimedia Appendix 2 presents the postcounseling survey instrument. A particular aim of this follow-up survey was to elicit women’s preferred choice of contraceptive method and the cited reasons for choosing this method immediately after counseling. Interviews with women and husbands who were present took no more than 15 minutes and were conducted privately in accordance with the standard interviewing procedures that were established for the baseline survey.

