#### Home-Based Survey

For women who did not visit the Good Health Kauma Clinic and who were also uncontactable by phone, the field team attempted to contact them at their homes up to a maximum of one time. Women who were reachable at their homes were invited to participate in a home-based follow-up survey, which was administered in person by a field enumerator. The home-based follow-up survey instrument took no more than 20 minutes in total and was identical to the clinic-based and phone-based follow-up survey instruments. The survey was administered in a private room at a woman’s home.

All protocols related to the consent process and in-person survey administration followed during the baseline survey were also followed for the clinic, phone, and home surveys. Before administering each survey, the field enumerators clearly explained the purpose of the follow-up to the respondents and asked for their consent to participate. For in-person clinic-based and home-based surveys, written consent from respondents was solicited, whereas verbal consent was obtained from participants who were contacted for the phone survey. Following the receipt of consent, the enumerators would then ensure the confidentiality and privacy of responses by asking the respondent to find a private room or space in their household (for the baseline, counseling, phone follow-up, and home follow-up surveys) or at the clinic (for clinic-based surveys) where their responses could not be overheard. For each woman, survey data were collected up to a total of 3 time points (at baseline, at the counseling stage, and at the follow-up stage).

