### Analysis Plan

The analysis of quantitative study data will be conducted using STATA and R (R Foundation), where appropriate. Descriptive analysis will be performed for all variables, and unadjusted comparisons between experimental arms will be conducted. Descriptive statistics, including frequencies, means, and SDs, will also be performed. Chi-square tests and one-tailed *t* tests will be used to examine associations in the data. A probability value of less than .05 will be considered statistically significant for all the statistical tests that are conducted. Continuous variables will be tested for normality, and nonnormal values will be categorized or appropriately transformed. Given our hypotheses regarding the impact of our intervention on our key outcomes, one-sided hypothesis tests will be conducted for all our main analyses.

Our main econometric specifications will (1) estimate the intent-to-treat (ITT) effects of our family planning intervention on fertility intentions and preferences, contraceptive intentions and preferences, intention to switch methods, and other outcomes related to contraceptive behaviors by directly regressing our outcomes of interest on a binary variable indicating receipt of the intervention and (2) estimate the effect of interventions on downstream behavioral outcomes (such as women’s uptake of contraceptive options and the concordance between their revealed preference and their stated preference) using a 2-stage least squares model, in which the intermediate counseling variable will be instrumented by the treatment. The main econometric specification for estimating the ITT effect of our family planning intervention is defined as follows:

*Y_it_* = *β_0_* + *β_1_T_it_* + *X_it_ζ* + *Y_i0_* + *η_i_* + *ε_it_*

where *Y_it_* is the outcome variable of interest for woman 𝑖 in time period 𝑡=0, 1, 2 for baseline (time period 0) and follow-up (time periods 1 and 2), respectively; *T_it_* is an indicator of assignment to 1 of the 3 treatment arms; *X_it_* is a vector of individual-level covariates that are controlled for in the analysis; η_i_ is the individual-specific fixed effect; *Y_i0_* is the baseline level of the outcome; and *ε_it_* is the error term. Here, the outcome variables of interest include immediate, intermediate, and long-term outcomes described in the previous sections.

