#### Intention to Switch Methods: Partner Invitation Interventions

Our measure of a woman’s intention to switch to another contraceptive method is proxied by her answer to the question, “if you had the choice and ability to switch to another family planning method, would you choose to switch?” An intervention to encourage women to invite their husbands or male partners to counseling could have 2 potential effects on women’s stated preferences for family planning methods. On the one hand, male involvement in counseling may encourage women to change their contraceptive preferences by allowing women to more actively retain and interpret counseling messaging [15,16] and through increased communication between partners [20]. On the other hand, male involvement in counseling might discourage women from changing their stated preferences if they feel compelled to hide their true preferences from their partners [41]. On the basis of the existing evidence on male involvement, we hypothesize that male involvement in counseling is likely to increase a woman’s intention to switch methods. Assuming an attrition-adjusted sample of 700 women, with 400 women assigned to partner invitation arms, T1 and T3, compared with 300 women assigned to noninvitation arms, T0 and T2, we will have 86% power to detect a 10 percentage point increase in women’s intention to switch methods in the intervention arm from 20% to 30% (α=.05, two-sided). If, instead, we use a one-sided test, then we estimate that we would have 92% power to detect the same 10 percentage point increase in intentions to switch.

Table 5 presents the levels of power (1−β) that could be achieved for various minimum effect sizes for the likelihood of women’s intention to switch contraceptive methods, assuming a baseline switching rate of 20% in both the intervention and control arms and a fixed endline sample size of 700 women.

**Table 5 table5:** Power calculations for intentions to switch methods, partner invitation intervention.

Control likelihood, n (%)	Intervention likelihood, n (%)	Significance level, α	Control sample size, n	Intervention sample size, n	Power
60 (20)	112 (28)	.05	300	400	0.69
60 (20)	116 (29)	.05	300	400	0.78
60 (20)	120 (30)	.05	300	400	0.86
60 (20)	124 (31)	.05	300	400	0.91

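### The main model labels the counseling-stage wave as follow-up, but contraceptive use and pregnancy status at that wave are recorded before counseling; stacking both periods under one coefficient dilutes the effect on use

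*Protocol article*

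**What the plan says.** The main specification (Analysis Plan) regresses the outcome on an assignment indicator with one coefficient, covariates, the baseline outcome and an individual fixed effect. Its time index runs 0, 1, 2, described as "for baseline (time period 0) and follow-up (time periods 1 and 2), respectively". It is said to serve immediate, intermediate and long-term outcomes alike.

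The waves are described elsewhere:

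- Study Sample and Inclusion Criteria: "One follow-up survey was conducted after the intervention and was administered to women either at the clinic or on the phone".
- Home-Based Survey: "survey data were collected up to a total of 3 time points (at baseline, at the counseling stage, and at the follow-up stage". Follow-Up Phased Rollout likewise describes a panel with three observations per woman.
- Table 3 marks contraceptive use and pregnancy and fertility outcomes as collected at baseline, counseling and follow-up.
- Intervention Protocols: "A precounseling survey was administered to each woman, where they were asked to confirm their personal information", covering "pregnancy status, current contraceptive use, and preferences for fertility and contraception".
- Survey Instrument and Rollout: a particular aim of the postcounseling survey was to "elicit women’s preferred choice of contraceptive method and the cited reasons for choosing this method immediately after counseling". Current use is not mentioned there.
- Postcounseling Package of Services: transport and reimbursement are offered after the postcounseling survey, for one month.

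**The concern.** Two of the three time points carry the label follow-up, but only one follow-up survey exists. The other time point is the counseling stage, where current use and pregnancy status come from a survey taken before the session. Even an answer given at the end of a session of at most one hour could not reflect a clinic visit, because the clinic package had not yet been offered.

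For these outcomes the period 1 value is in effect a second pre-intervention measurement. Counting it as post-intervention under a single coefficient averages a zero with the effect at follow-up. Contraceptive uptake is one of the two outcomes on which the study is powered, so a real effect on it could be understated or missed.

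**Working it through.** **1. Identify period 1.** The waves are baseline, counseling stage and one follow-up. With period 0 as baseline and period 2 as the follow-up survey, period 1 can only be the counseling stage.

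**2. Reproduce the plan's power.** Inputs from Contraceptive Prevalence: Partner Invitation Interventions: 50% v 60%, 300 v 400 women, α = .05.

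- Pooled proportion = (150 + 240)/700 = 0.557. SE under the null = √[0.557 × 0.443 × (1/300 + 1/400)] = 0.0379. SE under the alternative = √(0.25/300 + 0.24/400) = 0.0379.
- Two-sided power = Φ[(0.10 − 1.96 × 0.0379)/0.0379] = 0.751 (stated 75%).
- One-sided power = 0.840 (stated 85%, within 2 points).

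The plan's figures describe a single-wave comparison.

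**3. Size of the dilution.** Least squares was applied to noise-free expected outcomes, 400 treated and 300 control, with effect 0 at t=1 and 10 points at t=2.

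| Specification | Estimated effect |
|---|---|
| t=2 only | 10.0 points |
| t=1 and t=2, treatment on at both, fixed effects with or without period effects | 5.0 |
| t=1 and t=2, comparison over the two post-baseline waves | 5.0 |
| As the two rows above, with 51/782 = 6.5% missing at t=2 | 4.75 to 4.83 |
| Time-invariant assignment stacked over t=0, 1, 2, no fixed effects | 3.3 |
| Time-invariant assignment with individual fixed effects | not identified |

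By hand: (0 + 10)/2 = 5 and (0 + 0 + 10)/3 = 3.3. If fixed effects are fitted without period effects, a common drift also enters: a 5-point rise in both groups at t=2 moves the 5.0 to 7.5.

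**4. Power with baseline adjustment.** The equation contains the baseline outcome, so the variance should reflect it. Assume a common within-woman correlation r between any two waves and variance 0.25 in both groups. The unadjusted SE is s = √(0.25/300 + 0.25/400) = 0.0382.

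- Pooled: SE = s × √[(1 + r)/2 − r²], effect 0.05.
- Follow-up only: SE = s × √(1 − r²), effect 0.10.
- Power = Φ(effect/SE − z), with z = 1.96 two-sided or 1.645 one-sided.

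| r | Pooled SE | Pooled power, two-sided (one-sided) | Follow-up SE | Follow-up power, two-sided (one-sided) |
|---|---|---|---|---|
| 0.2 | 0.0286 | 42% (54%) | 0.0374 | 76% (85%) |
| 0.5 | 0.0270 | 46% (58%) | 0.0331 | 86% (92%) |
| 0.8 | 0.0195 | 73% (82%) | 0.0229 | 99% (over 99%) |

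The one-sided figures matter most, because the Analysis Plan makes its main tests one-sided. The documents do not give r, hence the range.

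**The case against.** The strongest reply is that the article never says that both periods are stacked for every outcome. It prints one generic equation, speaks of outcomes at different horizons, and may leave the mapping of outcomes to waves to a fuller plan. It names uptake and concordance under the two-stage least squares specification rather than the intent-to-treat equation. Principal Findings says that data on realized preferences, including uptake, came from clinic visits and from phone or home follow-up, all of which come after counseling.

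This makes the dilution conditional, and part of the reply stands: the authors may intend to use follow-up alone for uptake. It does not remove the point. The label given to period 1 is wrong for use and pregnancy status on the article's own description, and nothing in the Analysis Plan restricts these outcomes to period 2. The intent-to-treat specification also covers other contraceptive behaviors, and a two-stage model that stacks the same waves has a reduced form diluted in the same way.

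Three stronger readings are tempting and are not supported:

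- **That the estimate is necessarily half the true effect.** The factor depends on how treatment is coded and which waves enter. The printed equation fixes neither.
- **That power falls to roughly 28-39%.** That range comes from the unadjusted mean of two waves and ignores the baseline outcome in the equation.
- **That intention to switch is damaged in the mirror-image way**, because women who have already switched would answer no to "if you had the choice and ability to switch to another family planning method, would you choose to switch". Any size for this needs switching rates that the documents do not give. A lower intention after switching is also a real effect at a later time, so which wave to use is a choice of estimand and not a bias.

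**Conclusion.** The point holds for contraceptive use and pregnancy status, and for outcomes derived from current use. Calling the counseling stage follow-up contradicts the article's own account of when these were recorded. If the equation is applied as printed to both periods, a 10-point effect at follow-up appears as about 5 points under the most natural coding and about 3.3 points under a three-wave stack. For the 5-point case, two-sided power is about 42-73% against 76-99% at follow-up alone; one-sided it is 54-82% against 85% to over 99%.

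These figures assume no effect at period 1, near-equal weight for the two periods, no uncontrolled time trend, and a within-woman correlation of 0.2 to 0.8. The zero at period 1 is firm for the counseling and the clinic package. For the husband invitation, which comes before the session, it also assumes that the encouragement alone does not change use before counseling. The point does not extend to outcomes asked after the session, such as the preferred method, for which period 1 is a genuine post-intervention measurement.

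**What to change.** In the Analysis Plan:

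1. Name period 1 as the counseling stage and period 2 as the follow-up survey.
2. Estimate contraceptive use, uptake, method switching, pregnancy status and realization of the ideal method at period 2 only, in both the intent-to-treat and two-stage least squares models. This agrees with Principal Findings.
3. Treat precounseling answers as pre-intervention values (for example as additional baseline covariates), not as outcomes.
4. Let outcomes asked after the session, such as the stated preferred method, keep period 1 as a post-intervention wave, preferably with a separate effect for each wave.

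The cost is a change of wording. All data are collected and the article reports that analyses are ongoing. Fewer records enter the models for use and pregnancy, but the records removed as outcomes carry no information on the counseling effect and remain usable for adjustment.

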
### Study Objectives

In this study, we identified the causal impact of user-centered approaches to family planning counseling on women’s contraceptive preferences and decision making by means of a randomized controlled trial. In particular, we investigated two channels that have been hypothesized to play a role in contraceptive decision making: (1) a preference-based, targeted, user-centered approach to family planning counseling and (2) male involvement in family planning counseling. To this end, we tested the following 2 hypotheses:

A preference-driven, tailored, user-centered approach to counseling would allow women to express and realize their contraceptive preferences more effectively.The involvement of male partners in family planning counseling may allow women to express their contraceptive preferences and, in turn, translate their preferences into behavior more effectively.

The study population comprised married women aged 18-35 years living in Lilongwe, Malawi. As part of the trial, each woman in the study was randomly assigned to 1 of the 3 treatment arms or a control arm. A woman assigned to one of the intervention arms received one tailored, user-centered counseling session, followed by a package of family planning services that was designed to reduce the key barriers to accessing family planning in urban Malawi. The primary objective of this study is to evaluate the impact of user-centered counseling on a woman’s contraceptive use, intention to change stated ideal methods, switching of the current method, and realization of the stated ideal method. Primary outcomes include changes to women’s contraceptive method preferences (both stated and realized) over time and changes to women’s contraceptive concordance (whether a woman’s stated choice of contraceptive method, her ideal method, is the method that she is, in fact, using). Secondary outcomes include changes to male partners’ fertility and family planning preferences, women’s sexual and marital well-being, and changes in women’s decision-making in the household.

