### Sample Size and Power Calculations

#### Target Sample and Key Outcomes

The sample size of this study was powered to primarily identify the independent effects of tailored family counseling and male involvement on women’s contraceptive uptake and switching of methods. On the basis of the preliminary power calculations for the primary outcomes of interest, our target baseline sample consists of 700 eligible women who consent to participate in the study. Among these 700 women, 100 women were assigned to the control arm T0, and 200 women were assigned to each of the 3 intervention arms, namely, T1, T2, and T3.

Previous studies have found that one-fifth of women of reproductive age were either pregnant or had given birth to a child in the past 6 months [40]. To meet our target sample size of 700 women who would be eligible to participate in our study, we need to recruit a total of 940 women if we conservatively assumed a combined ineligibility or refusal rate of 25%.

We have powered our study to detect effects on the following outcomes: (1) contraceptive uptake and (2) intention to switch from the current contraceptive method.

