### Study Limitations

Our study has several limitations. Although the study is powered to independently test the effects of 2 user-centered counseling procedures on women’s stated and realized preferences, the sample size of this study may be too small to allow for the examination of interaction effects across treatment arms. As an exploratory exercise, we will examine these effects and present them as supplementary findings. Moreover, although our study can infer the manner in which women realize their preferences in response to counseling, it is not as straightforward to be able to disentangle a woman’s true individual preferences for family planning from her stated preferences in the presence of her partner, who is likely to influence her eventually realized choice (or lack of choice) of method. To this end, additional research is warranted to better understand how women’s true preferences are expressed and can be documented, even in cases where their partner is present. Similarly, it would be equally necessary to further explore the trade-off that women face between (1) making independent decisions to reflect their individual preferences and (2) incorporating their husband’s/family’s preferences to make jointly/socially better-off, but not necessarily individually better-off, decisions.

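### The main ITT equation has a single treatment indicator, so it does not estimate the separate targeted-counseling and husband-invitation effects that the trial hypothesises and powers

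*Protocol article*

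**What the plan says.** All places are in the protocol article.

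- **Study Objectives** announces "we tested the following 2 hypotheses". One concerns counseling: "A preference-driven, tailored, user-centered approach to counseling would allow women to express and realize their contraceptive preferences more effectively". The other concerns husbands: "The involvement of male partners in family planning counseling may allow women to express their contraceptive preferences".
- **Randomization** crosses the two interventions. T0 has neither, T1 the invitation only, T2 targeted counseling only and T3 both. Allocation to T1, T2, T3 and T0 is 2:2:2:1 (planned 200, 200, 200 and 100).
- **Target Sample and Key Outcomes** says the sample was "powered to primarily identify the independent effects of tailored family counseling and male involvement on women’s contraceptive uptake and switching of methods".
- **The four power subsections (Tables 4–7)** use two contrasts only: T1+T3 against T0+T2 for invitation, and T2+T3 against T0+T1 for targeted counseling. Each compares 400 with 300 women.
- **Study Limitations** repeats that "the study is powered to independently test the effects of 2 user-centered counseling procedures" and treats interaction as exploratory.
- **Analysis Plan** describes the main ITT analysis as "directly regressing our outcomes of interest on a binary variable indicating receipt of the intervention". It prints one equation with one coefficient β1 on T_it, which "is an indicator of assignment to 1 of the 3 treatment arms". Main tests are one-sided. No main model with separate invitation and targeted terms appears anywhere in the article.

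**The concern.** The hypotheses and the sample size concern two factor effects. The printed main model has room for one. A positive β1 would not show which intervention worked. A β1 near zero could mean that neither worked, or that one helped and the other hindered. The comparison would also rest on T0, the smallest arm, instead of on margins of 300 and 400, so the quoted power would not describe the test being run. At stake is whether the analysis labelled as main can answer either stated hypothesis.

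**Working it through.** **Inputs.** Planned arms are T0 100 and T1, T2, T3 200 each. The base rates are 50% (contraceptive prevalence) and 20% (intention to switch), the effect is 10 points, and α is .05 (all from the power section). Below, a is the invitation effect and b the targeted-counseling effect.

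**Formula.** Two-proportion normal approximation: power = Φ[(|p2 − p1| − z·s0)/s1]. Here s0 = √[p̄(1 − p̄)(1/n1 + 1/n2)], with p̄ the pooled rate, and s1 = √[p1(1 − p1)/n1 + p2(1 − p2)/n2]. z is 1.960 two-sided and 1.645 one-sided.

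**Step 1: the plan's own figures, 300 v 400.**
- 50% v 60%: s0 = 0.0379, s1 = 0.0379. Power is 75.1% two-sided (stated 75%) and 84.0% one-sided (stated 85%).
- 20% v 30%: s0 = 0.0334, s1 = 0.0325. Power is 85.6% (stated 86%) and 91.7% (stated 92%).

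The power section is right for the contrasts it names. The mismatch lies in the equation.

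**Step 2: what β1 estimates if T_it means any arm v T0.** With no interaction, the differences from T0 are a in T1, b in T2 and a + b in T3. With equal numbers in the three arms:

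β1 = [200a + 200b + 200(a + b)]/600 = (2/3)(a + b)

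- a = 10, b = 0 gives 6.7 points; a = 0, b = 10 also gives 6.7.
- a = 10, b = 10 gives 13.3, larger than either effect.
- a = 10, b = −5 gives 3.3.
- a = 10, b = −10 gives 0, and so does the reverse.

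**Step 3: power of that contrast, 100 v 600.**

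| True situation | Rates compared | Two-sided | One-sided |
|---|---|---|---|
| One intervention works, 50% base | 50% v 56.7% | 24% | 34% |
| One intervention works, 20% base | 20% v 26.7% | 28% | 40% |
| Both work, 50% base | 50% v 63.3% | 71% | 81% |
| Both work, 20% base | 20% v 33.3% | 79% | 87% |

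First row: s0 = 0.0537, s1 = 0.0539, so two-sided power = Φ[(0.0667 − 1.960 × 0.0537)/0.0539] = Φ(−0.71) = 24%. With the arm counts reported in Results (108, 223, 225, 228), the first row becomes about 26% two-sided.

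**Step 4: the other reading, one arm at a time v T0, 200 v 100.** For 10 points, power is 38% two-sided and 50% one-sided at the 50% base, and 45% and 58% at the 20% base.

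**Step 5: two indicators fitted together.** Regress the outcome on Invite (1 in T1, T3) and Targeted (1 in T2, T3) with arms of 100/200/200/200. The diagonal element of (X′X)⁻¹ for each factor is 0.006. With outcome variance 0.25, the standard error is √(0.25 × 0.006) = 0.0387, and 0.10/0.0387 = 2.58. Power is Φ(2.58 − 1.960) = 73% two-sided and Φ(2.58 − 1.645) = 83% one-sided. Each coefficient returns its own factor's effect.

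**Step 6: why jointly.** Targeted counseling goes to 200 of the 400 invited women but to 200 of the 300 not invited. The raw invitation margin therefore estimates a + (1/2 − 2/3)b = a − b/6. If both effects are 10 points, each raw margin is 8.3. Fitting both indicators removes this.

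**The case against.** - **The legend is ambiguous.** Elsewhere the article speaks of 1 of the 3 arms when it means the particular arm a woman is allocated to, and the equation is a template for many outcomes. A per-arm reading is therefore possible. This stands in part: under it, the two-thirds formula and the offsetting do not apply. The binary variable and single β1 still favour the any-arm reading, and neither reading gives the powered contrasts (Step 4).
- **The power loss depends on the scenario.** A reader might infer that power always falls to about a quarter. It does not: that figure requires the other intervention to have no effect. If each has the 10 points assumed in the power section, two-sided power is 71% against 75%, and 79% against 86%. This objection stands. What remains in that case is that the effect cannot be attributed.
- **Cancellation is not what the plan expects.** A reader might infer that the evidence the article cites on male involvement points to a decrease. It does not. The power section cites one study with a decrease, but explains why this design differs and expects an increase. The Introduction cites studies suggesting increased use and calls the experimental evidence limited and mixed. Offsetting is a possibility the article leaves open, not a prediction.
- **The intended contrasts are named elsewhere, and an article condenses.** Both are true, and the power section makes the intention clear. But the equation is not omitted: it is printed as the main specification, and it disagrees with those contrasts. The unadjusted comparisons between arms are listed with the descriptive analysis and are not stated to be the two factorial margins.

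**Conclusion.** The point holds as a mismatch between the printed main model and the trial's hypotheses and power basis. On the more natural reading, β1 is two thirds of the sum of two effects. On the other reading, it is a single-arm effect on 300 women. Under neither does it estimate the two 400 v 300 contrasts or carry the stated power. The failure to separate the two effects on the any-arm reading does not depend on effect size; the size of the power loss does.

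The figures assume no interaction, the planned arm sizes, the article's base rates and effect, and no gain from covariates or baseline adjustment. With an interaction, one third of it would be added to β1. The documents do not support saying that the power calculation is wrong, or that the trial cannot test its hypotheses: the same 700 women support both tests once the model is aligned.

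**What to change.** In the Analysis Plan, replace T_it with two assignment indicators fitted in one model, Invite (T1, T3) and Targeted (T2, T3). Test each coefficient for its own hypothesis. Keep Invite × Targeted as the exploratory term already announced under Study Limitations. Any arm against T0 may stay as a secondary summary, labelled as such. Arm dummies with prespecified factorial contrasts would also resolve the mismatch, but the two-indicator form is the simplest one that roughly restores the stated power.

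The cost is one rewritten equation and legend, with no new data. There will be two main coefficients instead of one, read under the no-interaction assumption that the power calculation already makes. The article reports the primary analyses as ongoing, and the contrasts are already named in its power section, so the change can be made as an alignment with them.
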